## **14. Ethics approval**

### **14.1 Review of the ethics committee**

This study complies with the Declaration of Helsinki (revised in 2013) and the relevant regulations of Chinese clinical trials. The protocol and written informed consent must be submitted to the ethics committee, and written approval from the ethics committee must be obtained before the study can be formally conducted. The investigator must submit an annual report of the study to the ethics committee at least annually. The investigator must notify the ethics committee in writing when the study is discontinued and/or completed; the investigator must report to the ethics committee in a timely manner all changes occurring in the conduct of the study (e.g., revisions to the protocol and/or informed consent form) and must not implement these changes without first obtaining approval from the ethics committee, except for changes made to eliminate obvious and immediate risks to subjects. The ethics committee will be informed when this occurs.

### **14.2 Informed consent**

The investigator must provide the subject or his/her legal representative with a readily understandable and ethics committee - approved informed consent form and allow

Version: 1.1  
Date: 2021.03.15

sufficient time for the subject or his/her legal representative to consider the study, and the subject will not be enrolled in the study until signed written informed consent has been obtained from the subject. Subjects will be provided with all updated versions of the informed consent form, along with written information, for the duration of the subject's participation. The informed consent form should be retained for review as an important document of the clinical trial.

## **15. Confidentiality measures**

The results of the study may be published in medical journals, but we will maintain the confidentiality of the patients' information in accordance with the requirements of the law, and the personal information of the patients will not be disclosed unless it is required by the relevant laws. When necessary, the government administration and the hospital ethics committee and its related personnel can access the patients' information according to the regulations.

## **16. Proposed study timelines**

This study is estimated to take about 4 years including patients' recruitment for 1.5 years. This study is expected to be conducted between October 2020 and September 2024.

## **1. Introduction**

This Statistical Analysis Plan (SAP) describes the statistical analyses to be performed for the data from the protocol of a clinical trial entitled “Comparison of left bundle branch pacing and biventricular pacing in the treatment of chronic systolic heart failure with left bundle branch block: a multicenter, prospective, randomized, controlled trial” sponsored by Department of Cardiology, Zhongshan Hospital of Fudan University, Shanghai Institute of Cardiovascular Diseases, National Clinical Research Center for Interventional Medicine, Shanghai, China. This SAP is written based on the Protocol Version 1.0 (Date: 09 Aug 2020).

## **2. Study Objectives**

This study aims to evaluate the clinical outcomes of left bundle branch pacing (LBBP) versus biventricular pacing (BVP).

## **3. Study Design**

This a multicenter, prospective, randomized, controlled trial which enrolling patients with HF, left ventricular ejection fraction (LVEF)  $\leq 35\%$ , and left bundle branch block (LBBB). Patients will be randomly assigned in a 1:1 ratio to receive either LBBP or BVP. Follow-up visits will be conducted at 1 month, 3 months, 6 months and every 6 months thereafter after surgery to evaluate the clinical endpoints (including primary and secondary endpoints) of the two groups.

## **4. Study Arms**

All enrolled patients will receive either LBBP or BVP.

## **5. Randomization and Masking**

This study is a prospective, multicenter, randomized, single-blind trial. All enrolled patients will be randomly assigned in a 1:1 ratio to receive either LBBP or BVP. The research assistants who collect study outcome data will be masked to the participants' intervention assignment. All the efficacy and safety end points will be independently adjudicated by a committee whose members are unaware of the trial-group assignments and the identity of the patients.

## **6. Study Endpoints**

### **5.1 Primary endpoint**

The primary endpoint is the composite of all-cause mortality and heart failure hospitalization (HFH). HFH is defined as any urgent visit with heart failure (HF) signs or symptoms requiring intravenous diuretic therapy.

### **5.2 Secondary endpoints**

The Secondary endpoints including: (1) Individual outcomes of all-cause mortality; (2) individual outcomes of HFH; (3) Echocardiographic response/super-response rates at 6-month follow-up. Echocardiographic response is defined as an absolute improvement in left ventricular ejection fraction (LVEF)  $\geq 5\%$ . Super-response is

defined as an absolute improvement in LVEF  $\geq 15\%$  or improvement of LVEF to  $\geq 50\%$ .

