# 7. Data collection and follow-up

Baseline data including age, gender, etiology (nonischemic cardiomyopathy or not), comorbidities (hypertension, diabetes mellitus and etc.), NYHA functional class and current medications (angiotensin-converting enzyme inhibitors/ angiotensin II receptor blocker/ angiotensin receptor-neprilysin inhibitor, beta-blockers, spironolactone) will be collected at enrollment.

Type of device (cardiac resynchronization therapy with defibrillator or with pacemaker) and electrocardiographic measurements (intrinsic QRSd and paced QRSd) will be collected at implantation, and the intrinsic QRSd and paced QRSd are measured at speed of 100 mm/s from the onset to the end of QRS complex.

All enrolled patients will be routinely followed up at 1-, 3-, and 6-month post procedure and every 6 months thereafter in the device clinic. Pacing threshold is collected at implantation and follow-up. Echocardiographic measurements including LVEF, left ventricular end-diastolic diameter (LVEDD) and left ventricular end-systolic diameter (LVESD) will be collected at implantation and follow-up.

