## **7. Data management**

### **7.1 Case report form**

All data including screening assessments, examinations, therapeutic effects and safety assessments, will be documented in the participant's case report form (CRF). All CRFs for each patient should be collected and documented by study group members in a timely manner. Each CRF should be double-checked for missing data or potential errors, and will be stored in the study office.

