## 8.3 Statistical analysis

All analyses in this study will be conducted according to the intention-to-treat principle. Student's t-test is performed for normally distributed continuous variables while Wilcoxon signed rank test is for non-normally distributed data. The chi-square test or Fisher exact test is used for categorical variables. A two-sided P-value  $< 0.05$  is considered statistically significant.

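### The SAP gives no rule for patients who die or have no 6-month echo in the LVEF response endpoints, and the unadjusted, dichotomised test uses the echo data inefficiently

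*Supplement*

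**What the plan says.** SAP section 5.2 (Secondary endpoints) names "Echocardiographic response/super-response rates at 6-month follow-up". Response is an absolute LVEF gain of at least 5%. Super-response is a gain of at least 15% or an LVEF reaching at least 50%. The section does not say which echo the gain is measured from.

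SAP section 8.3 states "The chi-square test or Fisher exact test is used for categorical variables" and "All analyses in this study will be conducted according to the intention-to-treat principle". No adjusted model appears in the SAP or in protocol v1.1. The SAP's only mention of missing data is in section 7.1: "Each CRF should be double-checked for missing data or potential errors". That is a data-quality check and not an analysis rule.

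Protocol v1.1 section 7 schedules the echo data: "Echocardiographic measurements including LVEF, left ventricular end-diastolic diameter (LVEDD) and left ventricular end-systolic diameter (LVESD) will be collected at implantation and follow-up". LVEF is not in that section's list of items collected at enrolment. Section 5.1, however, requires LVEF of 35% or less for entry, so a qualifying value exists for every patient.

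**The concern.** A patient who dies before 6 months, withdraws or misses the visit has no LVEF gain to classify. With no rule, such a patient cannot enter a two-by-two table, and the analysed set becomes survivors with an echo. The plan itself expects losses: its sample size section assumes 10% dropout, and composite event rates (death or HF hospitalisation) of 10% with LBBP and 25% with BVP. If those who do not reach the echo differ in number or prognosis between arms, the response comparison no longer compares the randomised groups.

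Two lesser matters go with this. The echo that serves as baseline is undefined, and with a 5-point threshold that choice can decide whether a patient counts as a responder. Cutting LVEF at a threshold and ignoring baseline LVEF also leaves information unused.

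**Working it through.** The documents give no expected response rate, SD, missing fraction or power for the echo endpoints, so there is no figure of the plan's own to reproduce. All echo inputs below are assumptions. From the documents come only 100 patients per arm, two-sided alpha of 5%, the 5 and 15 point thresholds, and 10% dropout (hence 90 per arm with an echo).

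**1. Effect of the missing-data rule.** Assume response of 70% (BVP) and 85% (LBBP) among patients with an echo. The complete-case difference is 85 − 70 = 15.0 points whatever the missing fractions are. If every missing patient counts as a non-responder, the difference is 0.85 × (1 − m_L) − 0.70 × (1 − m_B), where m_L and m_B are the missing fractions in the LBBP and BVP arms:

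| Missing BVP | Missing LBBP | Calculation | Difference |
|---|---|---|---|
| 10% | 10% | 76.5 − 63.0 | 13.5 points |
| 15% | 5% | 80.75 − 59.5 | 21.3 points |
| 5% | 10% | 76.5 − 66.5 | 10.0 points |

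Extreme bounds with 10% missing in each arm:
- All missing BVP patients respond and no missing LBBP patients do: 76.5 − (63.0 + 10) = 3.5 points.
- The reverse: (76.5 + 10) − 63.0 = 23.5 points.

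These figures show how far the rule can move the result. They do not forecast what the fix below would give, because that fix counts only deaths as non-response.

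**2. Cost of dichotomising.** Assume normally distributed LVEF change, SD 10, mean 8 (BVP) and 12 (LBBP), 90 per arm.
- Response, P(change ≥ 5) = Φ((mean − 5)/10): Φ(0.3) = 0.62 and Φ(0.7) = 0.76.
- Two-proportion test: difference 0.140, standard error 0.069 under the null and 0.068 under the alternative. Power = Φ((0.140 − 1.96 × 0.069)/0.068) = 53%.
- Two-mean test: standard error 10 × √(2/90) = 1.49, and 4/1.49 = 2.68. Power = Φ(2.68 − 1.96) = 77%.

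**3. Value of adjusting for baseline LVEF.** Simulation with 2,000 runs per scenario and 90 per arm. Baseline LVEF has mean 29 and SD 5, capped at 35. Mean gain is 12 points with BVP and 4 more with LBBP. Follow-up SD is 9. Power at baseline-to-follow-up correlations of 0.2 / 0.4 / 0.6:

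| Endpoint | Unadjusted test | Logistic regression, adjusted |
|---|---|---|
| Response | 46 / 52 / 60% | 48 / 54 / 61% |
| Super-response | 60 / 73 / 83% | 65 / 75 / 84% |

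ANCOVA on 6-month LVEF has 82 to 96% power across the same scenarios. With no treatment effect, the unadjusted test rejects in 5.0 to 5.5% of runs. Adjusting the binary test therefore gains about 1 to 5 points of power, and leaving it unadjusted does not bias the test.

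**The case against.** The strongest reply is that the plan is silent and not wrong. A reader might infer that it drops patients who die or lack an echo. No section says so, and section 8.3 commits every analysis to intention-to-treat. That is fair as to wording. But intention-to-treat does not say what outcome to give a patient who has none, and a chi-square test without such a rule falls back on the available values.

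A reader might also infer that the implantation echo is the endpoint baseline and that it is exposed to an unmasked operator. The documents do not support either. Protocol v1.1 section 7 is a collection schedule and not an endpoint definition. Protocol section 4.2 and SAP section 5 (Randomization and Masking) mask the staff who collect outcomes and the adjudicating committee, and nothing says that the implanter reads the echo. An echo at implantation, taken before pacing, would be a reasonable baseline. The obvious alternative, the qualifying echo, was selected for LVEF of 35% or less and is therefore open to regression to the mean, which can inflate response in both arms. What stands is that the plan does not name the baseline or its timing relative to pacing.

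Nor does omitting baseline LVEF bias a randomised comparison. A responder endpoint is a legitimate choice, the trial was not powered on it, and the gap between 53% and 77% comes from dichotomising alone. These points stand and limit the efficiency argument to a recommendation.

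**Conclusion.** The concern holds for one set of secondary endpoints. The SAP does not define how death or a missing 6-month echo is counted. Applied as written, the test is a complete-case comparison that does not meet the plan's own intention-to-treat statement. Bias is possible if missingness differs by arm; it is not shown. On the assumed rates the choice of rule moves a 15-point difference to between 10.0 and 21.3 points, which is enough to warrant fixing the rule before the data are seen.

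The unadjusted, dichotomised test is valid but inefficient. Adjustment recovers about 1 to 5 points of power and a continuous LVEF analysis considerably more, in both cases under assumed means, SDs and correlations. The primary endpoint and its log-rank analysis are not touched.

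**What to change.** Keep the response and super-response endpoints, and in SAP sections 5.2 and 8.3:

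1. Count death before the 6-month echo as non-response.
2. Multiply impute other missing 6-month LVEF from the scheduled echoes, then classify response.
3. Name one baseline echo, obtained before pacing starts and used the same way in both arms.
4. Analyse response and super-response by logistic regression adjusted for baseline LVEF, and also report the difference in rates, because the odds ratio alone is harder to read.
5. Add, as a supportive analysis, the 6-month LVEF difference by ANCOVA adjusted for baseline LVEF, with a 95% confidence interval. LVEF is not defined after death, so report the number of deaths by arm beside it.

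The cost is SAP wording and a little more analysis, with no new measurements. Response rates will come out slightly lower, and the ANCOVA adds one comparison, which should be labelled supportive.

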## 5. Study participants

### 5.1 Inclusion criteria

(1) Age 18 to 80 years; (2) sinus rhythm, complete LBBB; (3)  $LVEF \leq 35\%$  with New York Heart Association (NYHA) functional class II to IV despite receiving at least 3 months' guideline directed medical therapy; (4) expected survival time  $> 1$  year; (5) the residence is stable and can meet the requirements of follow-up during the study period.

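### Echo benefit is tested only as two yes/no cuts of 6-month LVEF change, each with roughly a quarter to a third less power than a comparison of LVEF itself

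*Supplement*

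**What the plan says.** - **Endpoints.** SAP 5.2 (Secondary endpoints, under the Study Endpoints heading) lists "Echocardiographic response/super-response rates at" 6 months as the third secondary endpoint. It then says: "Echocardiographic response is defined as an absolute improvement in left ventricular ejection fraction (LVEF", and sets the threshold at 5 points. Super-response is a gain of at least 15 points or an LVEF of at least 50%. Protocol version 1.1, section 9.2, has the same definitions.
- **Test.** SAP 8.3: "The chi-square test or Fisher exact test is used for categorical variables". Both echo endpoints fall under this rule. SAP 8.4 covers only the time-to-event comparison.
- **Continuous data.** SAP 8.3 also says "Student's t-test is performed for normally distributed continuous variables", with a rank test otherwise. The rule is generic and names neither LVEF nor a time point.
- **Data.** Protocol section 7: "Echocardiographic measurements including LVEF, left ventricular end-diastolic diameter (LVEDD) and left ventricular end-systolic diameter (LVESD) will be collected at implantation and follow-up".
- **Masking.** SAP section 5: "The research assistants who collect study outcome data will be masked to the participants' intervention assignment", and "All the efficacy and safety end points will be independently adjudicated by a committee whose members are unaware of the trial-group assignments".

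The documents give no expected LVEF effect, no SD of LVEF change, no reading error and no power figure for any echo endpoint.

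**The concern.** LVEF change is continuous, and the trial will hold the number for every patient with both echoes. Turning it into yes/no treats a gain of 6 points like one of 14, and a loss of 5 like a gain of 4. A test on the cut variable therefore needs more patients to see the same shift in LVEF.

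Protocol section 2 motivates the trial by non-response and absent reverse remodelling under BVP, so the echo result bears directly on the rationale. A real LVEF advantage of LBBP could be reported as no significant difference in response rate although the collected numbers would have shown it. An LVEF comparison added later under the generic t-test rule would not be a prespecified endpoint.

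**Working it through.** The plan has no echo power figure to reproduce; its sample size concerns only the primary endpoint. So the check compares the two analyses under stated assumptions.

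**Inputs from the documents.** 100 per arm less 10% dropout gives 90; two-sided 5%; cuts at 5 and 15 points; entry at LVEF of 35% or less. If the baseline reading is at most 35, reaching 50 already means a gain of at least 50 - 35 = 15, so super-response reduces to the 15-point cut.

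**Assumed inputs.** True gain 8 (BVP) v 12 (LBBP) points, SD of true change 9, single-reading error SD from 0 to 5. For the simulation, true baseline LVEF has mean 29 and SD 5.

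**1. No reading error, by hand.**
- 5-point cut: response is Φ((8-5)/9) = 0.631 for BVP and Φ((12-5)/9) = 0.782 for LBBP, a difference of 0.151; the mean rate is 0.706.
- Null SE = √(2 × 0.706 × 0.294/90) = 0.0679. Alternative SE = √((0.631 × 0.369 + 0.782 × 0.218)/90) = 0.0670.
- Power = Φ((0.151 - 1.96 × 0.0679)/0.0670) = 61%.
- Mean change: 4/(9 × √(2/90)) = 2.98; power = Φ(2.98 - 1.96) = 85%.
- Relative loss = (85 - 61)/85 = 28%. The 15-point cut gives the same, because 5 and 15 lie equally far from the midpoint of 8 and 12.

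**2. With reading error, by simulation (same inputs).**

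| Reading SD (assumed) | 5-point cut | Mean change | Relative loss |
|---|---|---|---|
| 0 | about 60% | 84% | 29% |
| 3 | 53% | 77% | 31% |
| 4 | 49% | 72% | 32% |
| 5 | 44% | 66% | 33% |

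The 15-point cut has 54%, 51% and 46% at SD 3, 4 and 5.

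**3. Other effect sizes, reading SD 3 to 5.**
- 3-point difference: 28-34% (5-point cut) v 43-53% (mean change).
- 5-point difference: 61-72% v 85-92%.

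**4. A second route that needs no SD.** Choose the effect so that the continuous test has 80% power with 90 per arm: a standardised difference of (1.96 + 0.842) × √(2/90) = 0.418. Power of the cut then depends only on the BVP response rate. Protocol section 2 suggests about 70% (30% do not respond) or under 60% (over 40% without reverse remodelling). These are proxies, since response is not defined there.

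| BVP response | LBBP response | Power of the cut | Relative loss |
|---|---|---|---|
| 50% | 66% | 60% | 25% |
| 60% | 75% | 57% | 29% |
| 70% | 83% | 52% | 35% |
| 80% | 90% | 43% | 46% |

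If the continuous test has 90% power, the cut has 69% at 60% response and 63% at 70%, a loss of 23-30%.

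**5. Information kept by a cut.** Relative efficiency is φ(z)²/[p(1-p)], where z is the normal quantile of the response rate p: 0.62 at 60% and 0.58 at 70%. So 38-42% of the information is lost.

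**6. Both cuts together.** In the 4-point setting, at least one of the two yes/no tests is significant in about 63-78% of trials over reading SD 5 to 0, without multiplicity correction, against 66-84% for mean change.

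**The case against.** - **Response is the clinical question.** Protocol section 2 frames the problem as non-response, and response rates answer that directly. This stands, and is a reason to keep them as secondary endpoints rather than make them descriptive.
- **Two cuts are tested, not one.** This stands in part: the gap narrows as in step 6. But that gain comes from two uncorrected tests, and neither gives the size of the LVEF difference.
- **A continuous comparison is already possible.** The generic rule in SAP 8.3 allows one. It does not make it an endpoint or fix the time point or estimate.
- **Secondary endpoint.** No power is claimed for it, no stated figure is contradicted, and the primary analysis is untouched. All of this stands.

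A reader might infer two stronger things. The first is that the 5-point step equals echo reading error, so that noise is counted as response. The documents give no reading error. A patient with no true change would pass the cut 4%, 12%, 19% or 24% of the time at an assumed reading SD of 2, 3, 4 or 5, but that applies only to such patients. In the model above, true BVP response is 63.0% and measured response 63.5-64.6% at SD 3 to 5, and only 1-4% of measured responders have no true gain. Error also lowers the power of the continuous test, and under masking it should fall on both arms alike. Most of the loss is there with perfect readings. The second inference is that most of the information is discarded. At the BVP rates suggested by the protocol, 38-42% is lost, which is less than half.

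**Conclusion.** The point holds as one of efficiency. The only named echo endpoints are two dichotomies of a measure that is collected as a number, and each cut alone gives up roughly a quarter to a third of the power of a comparison of LVEF. The cause is the dichotomy, not reading error. The size rests on roughly normal LVEF change, 90 patients per arm with echo, and assumed gains and SDs that the documents do not state. It is smaller when both cuts are counted together, and larger if BVP response is 80% or more. This is a cheap and worthwhile improvement, not an error that invalidates the plan.

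**What to change.** - In SAP 5.2 and protocol 9.2, add the between-arm difference in 6-month LVEF as a named, tested secondary endpoint. Carry it into the protocol Summary, which also lists the endpoints.
- In SAP 8.4, state the analysis: a linear model of 6-month LVEF on arm and baseline (implantation) LVEF, reported as a mean difference with 95% CI.
- Keep response and super-response rates as secondary endpoints, tested as now.

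The cost is one more secondary test and a minor amendment to protocol and SAP, which under protocol 14.1 needs ethics approval before use. No visit, patient or measurement is added.

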## **7. Data management**

### **7.1 Case report form**

All data including screening assessments, examinations, therapeutic effects and safety assessments, will be documented in the participant's case report form (CRF). All CRFs for each patient should be collected and documented by study group members in a timely manner. Each CRF should be double-checked for missing data or potential errors, and will be stored in the study office.

